#### Mendelian randomization

We will use bidirectional, two-sample MR to interrogate putative causal directions for metabolic and anthropometric traits with high *r*_*g*_ for AN. SNP instruments for MR testing of disorder pairs will be selected based on *p* < 5 × 10^–8^ and *p* < 5 × 10^–6^, balancing power and weak instrument bias [94]. Inverse variance weighting (IVW) [95] is the basic method, and additional standard test considerations include Steiger filtering [96] for pleiotropic SNPs, adjusting for overlap between GWAS with MRlap [97], and FDR. To further account for weak instrument, confounding, and pleiotropic bias, we apply MR-Egger [98], MR PARS [99], and debiased IVW [100] and MR-APSS [101].

#### Power

Genetic correlations between ED diagnoses and metabolic traits have > 99% power, and PRS with all variants have 100% and > 85% power, at small *P*-value thresholds. Where PRSet assumes 50 causal pathways, power is > 80%, and where 100 causal pathways are assumed, power is > 90%. For MR, under the conditions that metabolic GWAS cases > 50 k, GWAS_METAB_ beta > 0.05, AN R^2^ of SNP on exposure > 0.05 and OR > 1.1, power analyses indicate > 80% power to discover bi-directional causal relationships between AN and metabolic traits. Finally, PheWAS analyses [102] have sufficient power as selected biobanks meet the requirement of either > 200 cases or > 1,000 individuals with quantitative traits.

### Risk prediction (Aim 3)

A key outstanding question in complex trait genetics is how individuals with high genetic risk remain resilient (i.e., disease-free), while others with low genetic risk may develop disease. Here, we will compare high ED-PRS cases to low ED-PRS cases, and high ED-PRS cases to high ED-PRS controls to characterize ED risk and protective factors and parse the ‘gene x environment’ relationship [9]. For case-case comparison, we will meta-analyze case samples from EDGI, EDGI2, UK Biobank, and other biobanks. Low PRS cases will be investigated for environmental contribution to disorder development in the absence of high genetic risk. We will perform PheWAS with the following comparisons: top decile vs. bottom decile cases, top decile vs. all other cases, and low decile vs. all other cases. As pathway risk aggregation can differ from genome wide PRS, we will also compare pathway-PRS in high and low PRS cases to identify pathways with notable contribution to genetic risk or resilience. Similarly, we will then compare high PRS cases to high PRS controls to identify potentially protective environmental and genetic factors against disorder development despite the presence of overall genetic risk.

Finally, we will repeat clustering analyses as described in *‘Patient Stratification (Aim 2b)’*, using PRS scores as clustering variables in place of phenotype clustering [103]. ED GWAS (ANGI, EDGI, EDGI2, and ARFID Genes and Environment [ARFID-GEN]) are combined for maximum sample size, and PRS will be calculated for ED behaviors, psychiatric co-morbidities, and metabolic traits for each sample. PRS curve is nonlinear (disproportionally greater in those with the greatest PRS burden [104–106]) and will thus be categorized into quartiles as ordinal variables, from which Gower distance matrices will be derived and used as input for clustering. Our primary analysis will be case-based clustering but will additionally expand to case–control and control-only clustering (controls: ≥ 30 years old, no lifetime ED symptoms) for a more robust investigation. Clusters will be compared for diagnostic and symptomatic prevalence, and we will repeat PheWAS as described for PRS decile comparisons above.

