**Methods:**

A total of 20,000 new participants (18,700 cases and 1,300 controls) will be ascertained from the United States (US), Mexico (MX), Australia (AU), Aotearoa New Zealand (NZ), Sweden (SE), and Denmark (DK). Comprehensive phenotyping and genotyping will be performed for participants in US, MX, AU, NZ, and SE using the EDGI2 questionnaire battery and participant saliva samples. In DK, case identification and genotyping will be through the National Patient Register and bloodspots archived near birth. Case–control and case-case genome-wide association studies will be conducted within EDGI2 and enhanced via meta-analysis with external data from the Eating Disorders Working Group of the Psychiatric Genomics Consortium (PGC-ED). Additional analyses will explore genetic correlations between eating disorders (EDs) and other psychiatric and metabolic traits, calculate polygenic risk scores (PRS), and leverage functional biology to evaluate clinical outcomes. Moreover, analyzing PRS for patient stratification and linking identified risk loci to clinically relevant phenotypes highlight the potential of EDGI2 for clinical translation.

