### Inclusion criteria

#### Case definitions

Participants from US, MX, AU, NZ, and SE will be selected based on self-reported lifetime Diagnostic and Statistical Manual of Mental Disorders-fifth edition (DSM- 5) criteria for AN, BN, BED, and/or ARFID via the ED100K.v4 ED online questionnaire, revised from the previous version (ED100K.v3) to include ARFID [2]. The ARFID portion contains items developed by the study team in addition to adapted, lifetime versions of the Nine Item ARFID Screen (NIAS) [5] and Pica, ARFID, and Rumination Disorder ARFID Questionnaire (PARDI-AR-Q) [6]. In MX, those recruited through the Comenzar de Nuevo clinic will be identified based on clinical diagnosis. In DK, cases of AN and BN will be identified using International Classification of Diseases – 10 th Revision (ICD-10) codes (F50.0, F50.1 for AN; F50.2, F50.3 for BN). DK will not include ARFID or BED as no ICD-10 codes exist for these disorders. SE will link participants to diagnostic records from the Swedish National Patient Register and Quality Register (Riksät) that have been validated through diagnostic interviews with acceptable reliability [7].

For US, MX, AU, NZ, and SE, longstanding and/or severe AN (restricting or binge/purge AN subtype) will be captured by the EDGI2 battery and include AN duration ≥ 5 years, lowest illness-related BMI ≤ 15, ≥ 3 treatment periods, and above age 20 at enrollment. Severe cases with rapid weight loss who attain very low body weights will also be included. DK will use the Anorexia Nervosa Register-based Severity Index (AN-RSI), which creates a systematic and weighted combination of age at onset, inpatient treatments, outpatient readmissions, treatment length, and illness duration [8]. Modifications to the AN-RSI definition may be made based on emerging research.

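### The Aim 3 PRS-decile contrasts among cases cannot separate environmental contribution from case misclassification, and should be repeated in cases with a recorded clinical diagnosis

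*Protocol article*

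**What the plan says.** All references are to the protocol article.

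- **Contrasts.** Under Risk prediction (Aim 3): "We will perform PheWAS with the following comparisons: top decile vs. bottom decile cases, top decile vs. all other cases", followed by the lowest decile against all other cases. The section says that low-PRS cases will be examined for what the environment contributes when genetic risk is not high.
- **Case pool.** "For case-case comparison, we will meta-analyze case samples from EDGI, EDGI2, UK Biobank, and other biobanks". How the biobanks define a case is not described.
- **Case entry.** Under Case definitions, cases in the US, Mexico, Australia, New Zealand and Sweden are "selected based on self-reported lifetime Diagnostic and Statistical Manual of Mental Disorders-fifth edition (DSM- 5) criteria", by online questionnaire. There are two exceptions. In Mexico, "those recruited through the Comenzar de Nuevo clinic will be identified based on clinical diagnosis". Denmark uses registers: "In DK, cases of AN and BN will be identified using International Classification of Diseases", with no BED or ARFID cases.
- **External check.** "SE will link participants to diagnostic records from the Swedish National Patient Register and Quality Register (Riksät) that have been validated through diagnostic interviews". No use of this linkage is stated for Aim 3.
- **Numbers.** The abstract states: "A total of 20,000 new participants (18,700 cases and 1,300 controls) will be ascertained". The 18,700 cases are not split by country or by source of diagnosis.

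**The concern.** A person wrongly labelled a case will tend to have a PRS nearer to that of non-cases. Picking labelled cases with a low PRS therefore also picks, to some degree, people who are not cases. A labelled case with a low PRS is what an environmentally driven illness would produce, and it is also what a false positive would produce. The contrast as described cannot tell them apart.

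Any trait on which true and false cases differ, such as treatment history, severity, comorbidity or reported life events, would then differ between PRS deciles without aetiological meaning. The FDR correction described under PheWAS deals with multiplicity and leaves this bias untouched. Pooling more cases makes a spurious difference more significant and does not make it smaller. At stake is what Aim 3 can claim about risk and resilience factors in low-PRS cases.

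**Working it through.** The protocol article prints no figure on this point, so there is none to reproduce. Its totals agree: 18,700 + 1,300 = 20,000.

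**Inputs from the article.** Contrasts in PRS deciles. Expected meta-analysis cases of about 47,000 (AN), 16,000 (BN), 10,000 (BED) and 6,500 (ARFID), so a tenth is at most about 4,700, 1,600, 1,000 and 650. The size of the Aim 3 case pool itself is not given.

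**Assumed inputs, none from the article.** Prevalence K = 2%; liability variance explained by the PRS, R² = 2% or 5%; share of labelled cases that are false, m = 10%; false cases with the PRS distribution of non-cases.

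**Step 1, model.** The PRS is standard normal. With t the upper-K normal quantile,

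P(case | PRS) = Φ((√R² × PRS − t) / √(1 − R²)).

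This gives the PRS densities f₁ (true cases) and f₀ (non-cases). Labelled cases follow (1 − m)f₁ + m f₀. Deciles are cut on that mixture, and the false-case share in a decile is the mass of m f₀ there divided by the mass of the mixture there.

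**Step 2, false-case share at m = 10%.**

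| Scenario | PRS gap, true minus false | Bottom decile | Top decile | Difference |
|---|---|---|---|---|
| R² = 2% | 0.35 SD | 16.7% | 5.5% | 11.2 points |
| R² = 5% | 0.55 SD | 21.8% | 3.8% | 18.0 points |
| Gap set to 0.1 SD (two unit-variance normals) | 0.1 SD | 11.7% | 8.5% | 3.2 points |
| No gap | 0 | 10% | 10% | 0 |

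**Step 3, range.** Over K 1–4%, R² 1–10% and m 5–30%, with false cases having the PRS of non-cases, the bottom-decile share runs from 7% to 68% and the top-decile share from 1% to 22%. Between 13% and 33% of all false cases fall in the bottom decile, against 10% by chance. This is an enrichment of 1.3- to 3.3-fold, and most false cases lie in other deciles.

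**Step 4, what it does to a trait.** Assume, for illustration, a binary trait that differs by 40 percentage points between true and false cases, with overall frequency p = 0.3. The spurious difference is 0.40 × (difference in share), and z = difference / √(2 × 0.3 × 0.7 / n) with n cases per decile.

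- R² = 5%: 0.40 × 18.0 = 7.2 points; z = 2.8 at n = 650 and 7.6 at n = 4,700.
- R² = 2%: 0.40 × 11.2 = 4.5 points; z = 1.8 at n = 650 and 4.7 at n = 4,700.
- Gap 0.1 SD: 0.40 × 3.2 = 1.3 points; z = 0.5 at n = 650 and 1.3 at n = 4,700.

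Decile sizes are by disorder because the article analyses the disorders separately. A tenth of all 18,700 new cases (1,870) would pool them, and would also count Danish cases, who do not complete the questionnaire battery.

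**The case against.** **The article is condensed.** A sensitivity analysis by source of diagnosis could sit in an analysis plan that is not shown. That stands as a caution. But the article itself sets out both the contrasts and the use to be made of low-PRS cases, and nothing in it qualifies that use. The aim is worded as an investigation, which softens the point without removing it.

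**Two stronger readings are not supported.** A reader might infer that most recruited cases rest on self-report alone. That is plausible, but the Danish and Mexican-clinic numbers are not given, Swedish participants are also linked to registers, and US and Mexican sites recruit directly from treatment programmes. A reader might also infer that false cases gather in the lowest decile. They are over-represented there, but most lie elsewhere.

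**The PRS assumption is unfavourable to the plan.** People who pass a prescreen and a criterion-level lifetime questionnaire but are not true cases may be subthreshold or have another eating disorder. Their PRS would then be closer to that of cases. This stands: at a 0.1 SD gap the effect is small and would seldom reach significance, and at no gap it vanishes.

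**The confirmed subset is imperfect.** Denmark covers AN and BN only and lacks questionnaire data on life events. Restricting to recorded diagnoses also selects on treatment and severity, which are among the traits in question. Danish and Swedish raw data cannot be shared. All of this stands, and it limits how the check should be used.

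**Conclusion.** The concern holds as a conditional one. The direction follows whenever some labelled cases are false, the PRS discriminates, and false cases have a PRS nearer to that of non-cases. Under the stated assumptions (2% prevalence, 10% misclassified) the false-case share differs between bottom and top deciles by 11 to 18 points, falling to about 3 points at a 0.1 SD gap and to zero with no gap. The article does not say where in that range the study lies. It therefore does not show that the low-PRS findings will be artefacts, only that the contrast as described cannot exclude it. An added analysis is justified because the plan already holds cases with recorded diagnoses. Confidence in the size is low; confidence in the mechanism is reasonable.

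**What to change.** In Risk prediction (Aim 3), add a sensitivity analysis that repeats the decile contrasts, separately by disorder and with deciles re-cut, in cases with a recorded clinical diagnosis:

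- Swedish participants confirmed by National Patient Register or Riksät linkage;
- Mexican clinic cases;
- Danish AN and BN register cases, for register phenotypes only.

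Run it at the sites and meta-analyse the results where raw data cannot be shared. Report it beside the full-sample result, and describe low-PRS differences as environmental contribution only with that comparison shown. Do not use it as a veto. Where the confirmed subset is too small, which is likely for BED and ARFID, label the finding as unconfirmed.

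**Cost.** One repeated analysis on data that the plan already collects or links, with some coordination across sites. The subset is smaller and leans towards treated, more severe illness. Some true findings will not be confirmed, and attenuation there does not by itself prove misclassification.

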#### Aim 3: Evaluate genetic and environmental risk and resilience factors to inform risk prediction

Genetic or molecular groupings and patterns across cases and controls will be investigated through phenotypically characterizing individuals in the highest and lowest deciles of PRS based on clinical and phenotypic outcomes, and by genetically characterizing the top and bottom deciles of clinical severity across various PRS and PRS pathways. We will compare high-PRS cases with high-PRS controls to identify potentially protective environmental and genetic factors.

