##### GWAS

GWAS will be performed by ancestry groups for each primary ED diagnosis, component behaviors, and dimensional traits captured through the EDGI2 battery. Binary and continuous GWAS will include correction for relevant covariates including sex, age, and genotype-derived principal components (PC) to correct for population stratification. The number of appropriate PCs will be determined using PCAiR.

For each ED, ancestry-specific EDGI2 GWAS will be meta-analyzed using MR-MEGA [49]. Where possible EDGI2 cohorts will be meta-analyzed with PGC-ED GWAS summary statistics, and any other publicly available ED GWAS summary statistics. In total, meta-analyses are expected to yield ~ 80,000 cases and ~ 730,000 controls (case-specific breakdown: AN≈47,000; BN≈16,000; BED≈10,000, ARFID≈6,500). By the time of analysis, additional cases may be contributed from independent international sites. Significant GWAS loci will be identified through standard per-GWAS Bonferroni correction and a conditional false discovery rate (FDR) approach across GWAS to identify shared loci [50].

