##### Polygenic Risk Score

PRS aggregate risk alleles across the genome, weighted for effect size, to provide an estimate of an individual’s risk for a disorder or trait. We will compare two methods, the classical *P*-value thresholding method and SBayesRC [57], and implement appropriate cross-population approaches, for example PRS-CSx [58]. Exclusion criteria for *P*-value thresholding include uncommon SNPs (MAF < 0.01), low quality variants (imputation INFO score < 0.7), indels, strand ambiguous SNPs, and SNPs within the highly variable extended MHC region (chr6:25–34 Mb). As standard, SNPs will be LD pruned and clumped. *P*-value thresholds are predefined (0.001, 0.01, 0.05, 0.1, 0.5). We will use SBayesRC to calculate PRS while modeling LD.

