#### Pathway specific PRS

Pathway PRS is an extension of PRS that identifies how risk alleles aggregate in particular gene pathways and enables inference of mechanisms of genetic risk conferral. We will use PRSet [91] and established gene set repositories including GO, SynGO, KEGG, and REACTOME for cohort specific analysis, and validate findings against UK Biobank. We will perform single and multiple pathway associations within each ED and assess proportion of variance explained with a nested approach. All analyses will be corrected for ancestry PCs, age, and sex [92].

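### Aim 3 compares pathway-PRS between cases sorted on a genome-wide PRS that contains those pathways, so a difference does not by itself show a notable contribution to risk or resilience

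*Protocol article*

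**What the plan says.** The statement of Aim 3 plans "phenotypically characterizing individuals in the highest and lowest deciles of PRS". Risk prediction (Aim 3) then sets the case-only groupings for the PheWAS: "top decile vs. bottom decile cases, top decile vs. all other cases, and low decile vs. all other cases". The next sentence adds the pathway step and its purpose: "we will also compare pathway-PRS in high and low PRS cases to identify pathways with notable contribution to genetic risk or resilience". The reason given is that risk may build up differently within pathways than over the whole genome.

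Two earlier sections define the scores. Polygenic Risk Score states: "PRS aggregate risk alleles across the genome, weighted for effect size". Pathway specific PRS states: "Pathway PRS is an extension of PRS that identifies how risk alleles aggregate in particular gene pathways", and names the tools: "We will use PRSet [91] and established gene set repositories including GO, SynGO, KEGG, and REACTOME". For the Aim 3 pathway step the article gives no reference value for a notable contribution, no score that omits the tested pathway, and no adjustment for the genome-wide PRS.

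**The concern.** The groups are formed on a total, and the quantity then compared is one component of that total. Cases in the top decile have, on average, a higher value of nearly every component that carries weight, because that is how they came to be in the top decile. Disease status is the same in both groups, so the contrast cannot show that a pathway separates affected from unaffected people. It also cannot show resilience, since no unaffected person is in it.

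If the difference is read as evidence, pathways could be reported as contributing to risk or resilience merely because they belong to the score. FDR does not protect against this, because the hypothesis of equal means is false by construction. A replication cohort sorted in the same way would show the same differences and would appear to confirm them.

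**Working it through.** The article gives no figure for this comparison, so there is none to reproduce. The PRSet power figures under Aim 2c concern a different analysis and come without sample size, alpha or effect size.

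**Inputs from the article.** High and low groups are taken as deciles. The GWAS section gives the expected cases per disorder: "case-specific breakdown: AN≈47,000; BN≈16,000; BED≈10,000, ARFID≈6,500". These totals include external summary statistics, so they are upper bounds for samples with individual-level scores.

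**Assumptions.** SNPs are independent, the pathway has no specific effect, and both scores use the same weights. The number and size of gene sets are not given. Sets of 10 to 500 out of 20,000 equal units are assumed, so f runs from 10/20,000 = 0.05% to 500/20,000 = 2.5%.

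**Step 1: built-in difference.** The correlation between pathway-PRS and genome-wide PRS is √f. The mean of the top decile of a normal variable is 1.755 SD, so the top-to-bottom gap is 2 × 1.755 = 3.51 SD. The expected pathway difference is 3.51 × √f SD. The meaning of the weights does not enter.

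**Step 2: rejection rate for one pathway.** With N/10 cases per decile, z = 3.51 × √f / √(2/(N/10)). For f = 0.1% and N = 6,500 this is 0.111 / √(2/650) = 0.111 / 0.0555 = 2.00, which gives 52% rejection at two-sided 0.05.

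| f | Difference (SD) | 6,500 cases | 10,000 cases | 16,000 cases | 47,000 cases |
|---|---|---|---|---|---|
| 0.05% | 0.08 | 29% | 42% | 60% | 97% |
| 0.1% | 0.11 | 52% | 70% | 88% | 100% |
| 0.25% | 0.18 | 89% | 97% | 100% | 100% |
| 0.5% | 0.25 | 99% | 100% | 100% | 100% |

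**Step 3: many pathways.** This takes 5,000 null sets with sizes log-uniform from 10 to 500, top versus bottom decile. The share flagged is:

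| Cases | FDR 5% | Bonferroni |
|---|---|---|
| 6,500 | 80% | 43% |
| 10,000 | 88% | 55% |
| 16,000 | 95% | 66% |
| 47,000 | 100% | 91% |

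Under FDR, sets of 50 to 500 are flagged 99% to 100% of the time at 6,500 cases or more. If the two scores use different weights with correlation 0.7 (sets of 10 to 500), the FDR figures are 64% at 6,500 and 98% at 47,000. For the top decile against all other cases they are 67% and 98%.

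**Step 4: confirming the cause.** Genotypes were simulated with 20,000 independent SNPs, pure noise weights and 360 random sets of 10 to 500 SNPs. At 6,500 cases 78% of sets passed FDR, and at 18,700 cases 91% did. Cases were then re-ranked on the genome-wide PRS without the tested pathway. The share passing FDR fell to 0%, and the share with p < 0.05 fell from 80% to 4.4% and from 92% to 3.1%. The overlap therefore produces the excess.

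**Step 5: whether leaving the pathway out of the ranking is a remedy.** It removes the artefact but finds little. Under a liability model (assumed prevalence 1% to 3%, PRS R² 2% to 5%, a causal pathway with 1% of PRS variance, alpha 0.05), the case-only contrast has power of 5% to 6% at 6,500 cases and 6% to 12% at 47,000. At R² of 10% it reaches 9% and 32% to 33%.

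**The case against.** The article promises a comparison. It names no t-test, no zero-difference null, no alpha and no ranking rule, and a condensed article may leave the reference distribution to the full plan. The stated rationale could also mean a search for pathways that depart from the genome-wide ordering. This stands as far as the flagged percentages go: they are conditional on testing against zero. It does not rescue the contrast, because both the comparison and its inferential purpose are stated.

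Aim 2c already plans single and multiple pathway associations within each disorder, a nested assessment of variance explained, and validation in UK Biobank. Pathway inference in the study therefore does not rest on this one sentence, which lowers the severity. That nested step belongs to Aim 2c and is not invoked for the Aim 3 contrast.

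A reader might infer four stronger claims that the documents do not support:

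- **That almost every pathway would be flagged for every disorder.** This fits large samples or larger gene sets. For an ARFID-sized sample the range is 43% to 80%.
- **That 18,700 cases is the working sample.** The Abstract gives "A total of 20,000 new participants (18,700 cases and 1,300 controls", which pools four disorders that the plan analyses separately.
- **That the contrast is pure noise or simply ranks pathways by size.** The real weights come from case-control GWAS, so f carries some disease signal. Set size is a major driver but not the only one.
- **That the high-PRS case versus high-PRS control comparison has the same fault.** Both of those groups are selected in the same direction, so the artefact does not carry over in the same form. The article also does not explicitly mention pathway-PRS there.

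**Conclusion.** The point holds as a flaw in the stated contrast. Comparing pathway-PRS between high- and low-PRS cases cannot by itself identify pathways that contribute notably to risk or resilience, because a difference of about 3.51 × √f SD is expected whether or not the pathway matters. The algebra needs only approximate normality and independent SNPs. The shares flagged also depend on set sizes, usable cases per disorder, the multiplicity rule and how closely the two sets of weights agree, none of which the article fixes for this step. Severity is moderate: this is a secondary analysis within Aim 3, it touches no primary GWAS and no data collection, and it can be corrected before analysis.

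**What to change.** For pathway inference in Risk prediction (Aim 3), replace the case-only contrast with an outcome-based test:

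- Regress case-control status on the genome-wide PRS, with the pathway's SNPs and SNPs in LD with them left out, plus the pathway-PRS.
- Use samples independent of those that supplied the GWAS weights.
- Judge the pathway term against random gene sets matched on SNP number and LD, with FDR across pathways.

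If the high-versus-low case contrast is kept, label it descriptive and set each difference beside that of matched random gene sets. A case-only contrast with the pathway left out of the ranking should not be adopted as the means of finding pathways, because its power is low.

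The cost is a change of wording and extra computing. Fewer pathways will be reported. No new data are needed.

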### Patient stratification (Aim 2b)

Within-disorder heterogeneity, common in EDs, has both research and clinical implications [71–75]. Data driven taxonomy has improved disorder classifications previously [76]. We will mirror recent work using PRS to derive genetic clusters of schizophrenia phenotypic subtypes [77, 78] and apply advanced, unsupervised machine learning to group samples for clinically relevant outcomes, and compare these with ED PRS clusters. Standard steps include variable selection and normalization, Uniform Manifold Approximation and Projection (UMAP) [79] for dimensional reduction, and visualization and identify subgroups with HDBSCAN [80] density-based clustering. To ensure robustness and reliability, the clustering algorithm will be validated by applying the same procedures to both training and replication datasets (e.g., applying the same clustering algorithm across sites). Cluster similarity will be evaluated to assess the consistency and reproducibility of the clusters. Validated novel patient clusters will be compared to standard DSM-5 diagnoses with agreement matrices to identify whether clusters better explain clinical outcomes and heterogeneity, as well as demonstrate genetic diversity.

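### Coding each PRS into quartiles discards the upper-tail resolution that the article gives as its reason, and the ties it creates can produce grid-driven clusters in the HDBSCAN step

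*Protocol article*

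**What the plan says.** The section Risk prediction (Aim 3) ends with a clustering analysis that uses PRS as the clustering variables. Its inputs come from three families of traits: "PRS will be calculated for ED behaviors, psychiatric co-morbidities, and metabolic traits for each sample". The reason for the coding is that the "PRS curve is nonlinear (disproportionally greater in those with the greatest PRS burden"; each score "will thus be categorized into quartiles as ordinal variables, from which Gower distance matrices will be derived and used as input for clustering".

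The algorithm is taken from Aim 2b: "we will repeat clustering analyses as described in" that section. Patient stratification (Aim 2b) lists "Uniform Manifold Approximation and Projection (UMAP) [79] for dimensional reduction" and then the step to "identify subgroups with HDBSCAN [80] density-based clustering". Its check is to run the same procedure on training and replication data: "Cluster similarity will be evaluated to assess the consistency and reproducibility of the clusters". The Aim 3 clusters are then compared on diagnoses and symptoms and carried into a repeated PheWAS.

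Earlier in the same Aim 3 section, the PheWAS comparisons use finer cuts: "top decile vs. bottom decile cases, top decile vs. all other cases, and low decile vs. all other cases".

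The article does not state the number of PRS, the number of people clustered, the minimum cluster size, or whether UMAP is kept with the Gower input.

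**The concern.** There are two linked problems.

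1. **The coding defeats its reason.** If risk is concentrated at the top of the distribution, the distance between people should separate them best there. A quartile code does not separate them at all above the 75th percentile.

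2. **The coding suits the algorithm badly.** HDBSCAN looks for regions of high density. With p quartile-coded scores, people can occupy only 4^p positions, and everyone in the same position is at distance zero. A density method can take such a stack of ties for a cluster when the underlying scores have none.

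At stake is whether reported genetic subgroups are real. The same grid recurs in every dataset, so clusters that come from the grid can look reproducible across sites and then pass into the PheWAS.

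**Working it through.** The article gives no figure for this analysis, so there is none to reproduce.

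**Step 1. What the coding does to the tail.** Take a standardised, normally distributed PRS. The cut points are z(0.75) = 0.674 and z(0.90) = 1.282, with normal densities φ of 0.3178 and 0.1755.

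- Mean of the top decile: φ(1.282)/0.10 = 0.1755/0.10 = 1.75 SD.
- Mean of the 75th to 90th percentile: (0.3178 − 0.1755)/0.15 = 0.95 SD.
- Gap: about 0.81 SD before rounding. All of it is coded as zero distance.
- Share of the top code that lies outside the top decile: 15/25 = 60%.
- Gower distance on one score is |code difference|/3. Two people just either side of a quartile cut differ by 1/3. A person at the 76th percentile and one at the 99.9th differ by 0.

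**Step 2. Variance lost.** The within-quartile variances are 0.242, 0.037, 0.037 and 0.242. Their mean is 0.14, so about 14% of PRS variance is lost. The two outer quartiles account for 0.484/0.558 = 87% of that loss.

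**Step 3. A planted tail group.** In 3,000 simulated people, 150 (5%) were placed at +3 SD on every score, with minimum cluster size 30. Quartile codes merged them into a cluster of 310 (p = 2) or 184 (p = 3). Continuous scores recovered clusters of 152 and 150.

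**Step 4. Size of the grid.** 4^p is 64, 256, 1,024, 4,096 and 65,536 for p = 3, 4, 5, 6 and 8.

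**Step 5. Null simulation without UMAP.** The data are one multivariate normal with no clusters. Gower distance is the mean over scores of |code difference|/3, and the comparator is range-scaled continuous scores. The values of p, N, correlation and minimum cluster size are assumptions. Cells show the number of clusters, quartile codes against continuous scores.

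N = 3,000, r = 0.1, three seeds:

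| p | Minimum size 10 | Minimum size 30 |
|---|---|---|
| 3 | 64 v 2–4 | 64 v 0 |
| 4 | 186–201 v 0–2 | 0–3 v 0 |
| 5 | 17–35 v 0–2 | 2 v 0 |
| 6 | 2–17 v 0–2 | 0–3 v 0 |
| 8 | 3–5 v 0–2 | 2–3 v 0 |
| 10 | 2 v 0 | 2 v 0 |

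N = 18,700 (the new-case target, used only as a scale), r = 0.15, one seed, HDBSCAN neighbour setting fixed at 5:

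| p | Minimum size 10 | Minimum size 30 | Minimum size 100 |
|---|---|---|---|
| 4 | 256 v 5 | 256 v 2 | 52 v 0 |
| 5 | 944 v 2 | 164 v 2 | 43 v 0 |
| 6 | 509 v 3 | 87 v 2 | 44 v 0 |

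A further run at N = 6,000 (r = 0.15, one seed) gave 13–255 v 0–5 for p = 3 to 6, and 3–24 v 0–3 for p = 8.

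At p = 3 in the first table, and at p = 4 with minimum size 10 or 30 in the second, every cluster is exactly one grid cell. At larger p or larger minimum size, most are groups of cells.

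**Step 6. With UMAP first** (same kind of null data, N = 3,000 to 4,000). Quartile codes gave 64 clusters at p = 3 and minimum size 10, each a single cell. Continuous scores gave 74 there, and 38 to 88 across p = 2 to 8. At minimum size 75 continuous scores still gave 2 to 5. UMAP can therefore fragment structureless continuous data as well.

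**The case against.** The strongest reply is that the false-cluster result depends on settings an article may leave to the full plan. Three trait families could well mean six or more PRS. At N = 3,000 and minimum size 30, quartile codes give 0 to 3 clusters from p = 4 upward, and at N = 12,000, p = 5 and minimum size 120 they give 2. Aim 2b also lists UMAP, which Step 5 omits. With UMAP, continuous scores fragment too, so the contrast in Step 5 cannot be carried over to a pipeline that keeps it. The sample of 18,700 is not the clustering sample either: the section combines several studies, while the Analyses section says that some sites' raw data cannot be shared. All of this stands, and it limits the second problem to a conditional statement.

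It is also fair that the loss is local. The top quarter stays separate from the rest, about 86% of variance is kept, and the decile comparisons in the same section examine the tail directly. The plan compares clusters with DSM-5 diagnoses and clinical outcomes as well as replicating them, although none of these checks is a test against a no-cluster null.

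The reply does not reach the first problem. The coding, the distance and the reason are all fixed in the article, and the mismatch between them needs no assumption about p, N or UMAP.

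**Conclusion.** The point holds in two parts of different strength.

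- **Tail resolution: firm.** Within the clustering step, quartiles remove all resolution above 0.67 SD, contrary to the reason given for using them. The 0.81 SD gap and the 14% variance loss assume a normal PRS; the zero distance within the top quarter does not.
- **Grid-driven clusters: conditional.** Ties can produce many false clusters where continuous scores give few or none. Without UMAP the effect is strong for about 3 to 6 PRS and weaker for 8 or more, and it varies with N and minimum cluster size. The simulations use assumed settings and few seeds. Replication on the same coding would not expose the artefact.

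A reader might infer that HDBSCAN is bound to return nothing but cells of the coding grid, or that Aim 3 loses the high-PRS tail altogether. The article supports neither reading. Single-cell clusters need enough people per cell relative to the minimum size, and the decile PheWAS is unaffected.

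The step should be changed before analysis. It does not undermine the rest of Aim 3.

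**What to change.** 1. Replace the quartile coding with continuous PRS, standardised after residualising on cohort and ancestry principal components. Gower distance accepts numeric variables, so the rest of the step can stay. If emphasis on the tail is wanted, add a top-percentile indicator or a monotone transform.
2. State the number of PRS, the minimum cluster size, and whether UMAP is kept with the Gower input.
3. Run the whole pipeline, including UMAP if it is kept, on simulated single-Gaussian data with the same covariance. Accept clusters only if they exceed that null. This is needed even with continuous scores, because of the UMAP result in Step 6.

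The cost is a change of wording and a simulation, and possibly fewer reported clusters. No new data are needed.
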